### Primary and Secondary Outcome Measures

To measure the prevalence of IPV, our questionnaire will ask patients if their intimate partner had abused them physically, emotionally, or sexually in the past 12 months and throughout their lifetime. We believe that it is important that our study attempt to quantify levels of emotional and sexual abuse among our intended study sample because the various forms of IPV - physical, emotional, and sexual abuse - are concomitant with each other, and orthopaedic surgeons may serve as a second line of detection of IPV if victims are undetected in healthcare settings antecedent to their presentation to the orthopaedic clinic, such as the emergency department. Moreover, we take the stance that orthopaedic surgeons should be concerned about the holistic care of the individual instead of only being concerned with what is immediately treatable in their area of expertise. Therefore, to estimate the overall prevalence of IPV, we will combine the positive answers to the questions on physical, emotional, or sexual abuse.

We will also ask participants to complete two validated questionnaires that were designed for rapid assessment of IPV status in emergency departments, family practice, and women's health clinics that may be similar to our intended setting of an orthopaedic fracture clinic. We selected the Woman Abuse Screening Tool (WAST) and the Partner Violence Screen (PVS) for their psychometric properties, reliability, and specificity in identifying partner abuse. Moreover, a study that was published in 2006 reported that 94 percent of women who were administered both the PVS and WAST concurrently, as written questionnaires, considered them "easy" to complete [18]. Both questionnaires are widely used in IPV screening studies [18,20-26].

We chose to request that both questionnaires be administered to each participant to ensure that we are identifying all probable cases of IPV among women who attend orthopaedic clinics. In addition to the elucidation of physical abuse, the WAST contains questions that assess the levels of emotional and sexual abuse that we also feel are important to ascertain in our study, as mentioned previously.

Another research question that will be addressed in the study is what are patients' previous experiences and perceptions about discussing IPV with health care professionals. To that end, the questionnaire will also query the participant about her age, income, education, race/ethnicity, marital status, sexual orientation, and length of relationship. Additionally, participants will be queried about perceptions and previous experiences with reporting IPV in health care settings.

The questionnaire will also ask participants to record the characteristics of the injury that they are being seen for in the fracture clinic including: type of injury, how the injury occurred, locations of injury, and date of injury.

### Data Collection

The self-report component of the data collection will involve a written self-completed questionnaire. This method of data collection has been shown in a randomized trial to provide the least amount of missing data by the respondent and is generally favored over the use of a face-to-face interview or computer-based self-completed questionnaire [18].

A female study coordinator at each participating clinical site will approach all female patients who present to the fracture clinic for participation in this study. Due to the sensitive nature of the study, the informed consent process and completion of the questionnaire will take place in a private location by the female study coordinator. A screening form will be completed for all patients that will document their eligibility and whether they agree to participate in this study. After providing informed consent, the female study coordinator will provide the participant with the questionnaire to complete. When the participant has completed the questionnaire, she will place it in a sealed envelope and return it to the study coordinator. This process is described in Figure 2.

**Figure 2 F2:**
[figure not shown]
**Participant Enrollment Procedures**.

### Ethical Considerations

Due to the nature of the research topic, care must be exercised when recruiting individuals to participate in the study. Women are often afraid of disclosing that they are a victim of IPV for fear of retaliation from the offender, stigmatization by the individuals that she discloses to, embarrassment, and police involvement [27]. Because of this fear, key ethical issues addressed in this study are: 1) requirement for free and informed consent; 2) respect for privacy and confidentiality; 3) respect for justice and inclusiveness; 4) minimizing harm; and 5) maximizing benefit. Each of these items are discussed in greater detail below.

If an individual agrees to be approached by a study coordinator, the study coordinator will first ascertain whether the individual is eligible for participation and ask the participant if she would be able to accompany the study coordinator by herself to a private location to participate in a women's health survey. At no point during this initial contact will there be any mention of the words "abuse" or "violence." If the potential participant is able to come by herself into the private location, the informed consent process will be carried out, and the study coordinator will remain in the private location to ensure that the participant is not interrupted as she completes the questionnaire.

To maximize the opportunity for free and informed consent while respecting privacy and confidentiality, the informed consent process will only take place privately. Potential participants will not be invited to join the study if the study coordinator is not able to secure an opportunity when the individual is alone long enough to adequately explain the study and obtain informed consent. By approaching the potential participant in private, she also has the opportunity to provide free consent in the absence of significant others that may affect her decision to participate. Privacy and confidentiality will further be secured by assuring that research numbers will be used in the place of personal identifiers and that no medical personnel involved in the participant's care will know whether she participates in the study.

Justice and inclusiveness are respected by including all individuals who present to the orthopaedic fracture clinic that are relevant to the research question. Age restrictions are in place in light of possible legislative requirements within the geographic areas of the recruiting clinics, and exclusion criteria have been minimized to only those individuals who have a high likelihood of providing poor quality data or being unable to properly provide free and informed consent, given that the questionnaire is available only in the primary language of each participating site (i.e. English in Canada and the United States and Dutch in the Netherlands).

Harm will be minimized by respecting the participant's privacy and affirming to her that the care she receives is in no way affected by her decision to participate or not participate in the study. In addition, Dearwater et al. noted in their study that as a safety precaution women were only administered their questionnaire while in the absence of any friends, family, or medical staff [3]. We will adopt these criteria for our study as well.

To maximize benefit, individuals who are approached to participate in the study will be offered information resources pertaining to IPV and contact information of local IPV services in the clinic area. Fracture clinic staff will also be aware of the study and will also be provided with these materials in the event that the individual approached would prefer to speak to her care provider(s) about IPV instead of members of the study team.

### Protecting Against Sources of Bias

A bias towards under-reporting IPV is our primary concern. Considerations with respect to confidentiality will be addressed during data collection to reduce bias when participants are completing the questionnaire. Participants will be approached by a female study coordinator, and the consent process and the completion of the questionnaire will take place alone in a private location so as to reduce influence from others. Additionally, participants will be told that the survey is anonymous and will be instructed to not discuss the nature of this study with other participants, so as to increase reporting of IPV, if it exists, when completing the survey (participants may answer the questionnaire differently if they knew that they would be identified as IPV victims or non-IPV victims by the individual administering the questionnaire). Questions pertaining to the participant's demographics should be subject to minimal bias because the questions are categorical and are not intended to be subjective. An under-reporting bias is certainly possible; however, if our study finds an appreciable prevalence of IPV among respondents, we will have confidence that the likely "true" estimate is even higher.

Another source of potential bias in this study is that the questionnaire is self-administered as opposed to interview administered. This may result in some missing and inconsistent data. Due to the extremely sensitive and private information, as well as taking the women's safety into consideration, we believe that an interview-administered questionnaire is not appropriate. Due to the sensitive content of the questionnaire, the study coordinator will not check it over following completion therefore she will not be able to ask the patient about missing questions or inconsistencies.

An inherent limitation of this study which may produce bias is that non-participants may differ from participants in terms of demographics and abuse prevalence. Patients may be less likely to participate if they are a victim of IPV, thus resulting in a lower IPV prevalence rate. Also, some patients may decline to participate because they are not victims of IPV and as such feel that the issue is not relevant to them. Another limitation which may lower the reported IPV prevalence is that we may miss women who are severely injured as a result of IPV because we will not approach women who are taken to the fracture clinic by Emergency Medical Services. However, we may approach these patients at subsequent follow-up visits.

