In contrast to the use of mailed questionnaires, written self-reported surveys such as the questionnaire suggested in the proposed study design may have less likelihood of response bias. Use of such questionnaires has resulted in response rates between 62 percent and 95 percent among women who are invited into the study personally by research personnel and then administered the questionnaire if they chose to participate [1,4,18,19].

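### The expectation that the true prevalence exceeds the observed one holds only for under-reporting by respondents; with the selection biases the protocol itself lists, the net direction is unknown

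*Protocol article*

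**What the plan says.** All the statements at issue are in the protocol article, most of them in Protecting Against Sources of Bias.

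- The first paragraph opens with "A bias towards under-reporting IPV is our primary concern", describes the privacy and anonymity measures, and ends with the inference that "if our study finds an appreciable prevalence of IPV among respondents, we will have confidence that the likely 'true' estimate is even higher".
- The third paragraph turns to women who do not take part. It names one selection effect with its direction: "Patients may be less likely to participate if they are a victim of IPV, thus resulting in a lower IPV prevalence rate". It names a second without giving a direction: "some patients may decline to participate because they are not victims of IPV and as such feel that the issue is not relevant to them". It then adds a coverage problem: "Another limitation which may lower the reported IPV prevalence is that we may miss women who are severely injured as a result of IPV", with the remark that such women may be approached at a later visit.
- Rationale for an Observational Study Design cites "response rates between 62 percent and 95 percent among women who are invited into the study personally by research personnel".
- Data Collection provides a screening form for all patients that records eligibility and agreement to participate.

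The section does not weigh these effects against each other, and it does not return to the closing inference of its first paragraph.

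**The concern.** The inference treats the primary estimate as a probable lower bound. That needs either no upward bias or downward biases that outweigh it. Refusal by non-victims is an upward bias: it removes women without IPV from the denominator and so raises prevalence among respondents. The protocol lists this effect but neither states its direction nor lets it qualify the inference.

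Twelve-month prevalence is the primary objective. The hypothesis is that it is high enough to justify dedicated programmes, and the Discussion intends the result to support education of professionals and to inform a position statement. A figure of uncertain bias presented as conservative would carry more weight in that argument than it has earned. The sample of 3,600 does not help, since a larger sample narrows the interval around whatever value the selection produces.

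**Working it through.** **The plan's own figure.** The protocol attaches no number to the direction of bias. Its only precision figure, a 95% interval of 2.78% to 8.31% with 278 women, reproduces as the exact (Clopper-Pearson) interval for 14/278 = 5.04%. It is not affected by this point.

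**Inputs from the protocol.** Illustrative observed prevalence *p*: one third (pilot study) and 5% (Sample Size). Response range: 62% to 95%.

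**Assumptions.** The protocol gives no participation rate by IPV status and no disclosure rate. I let participation of victims (*rv*) and of non-victims (*rn*) lie anywhere from 62% to 95%, and the share of participating victims who disclose (*d*) from 70% to 100%, with no false positives.

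**Formulas.** The true share of victims among participants is *s* = *p*/*d*. The true prevalence in the eligible population is

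(*s*/*rv*) / (*s*/*rv* + (1 − *s*)/*rn*).

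It equals the observed *p* when *rv*/*rn* = [*s*/(1 − *s*)] / [*p*/(1 − *p*)]. Above that ratio, the true value is lower than the observed one.

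**Worked case,** *p* = 1/3, *d* = 1:
- *rv* = 0.95, *rn* = 0.62: 0.3509 / (0.3509 + 1.0753) = 24.6%.
- *rv* = 0.62, *rn* = 0.95: 0.5376 / (0.5376 + 0.7018) = 43.4%.

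**Break-even,** *p* = 1/3, so observed odds 0.5:
- *d* = 0.90: *s* = 0.3704, odds 0.5882, ratio 0.5882/0.5 = 1.18.
- *d* = 0.80: *s* = 0.4167, odds 0.7143, ratio 0.7143/0.5 = 1.43.

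**Full range:**

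| Observed | Disclosure | True, victims 95% / non-victims 62% | True, victims 62% / non-victims 95% | Break-even *rv*/*rn* |
|---|---|---|---|---|
| 33.3% | 100% | 24.6% | 43.4% | 1.00 |
| 33.3% | 90% | 27.7% | 47.4% | 1.18 |
| 33.3% | 80% | 31.8% | 52.3% | 1.43 |
| 33.3% | 70% | 37.2% | 58.2% | 1.82 |
| 5% | 100% | 3.3% | 7.5% | 1.00 |
| 5% | 90% | 3.7% | 8.3% | 1.12 |
| 5% | 80% | 4.2% | 9.3% | 1.27 |
| 5% | 70% | 4.8% | 10.5% | 1.46 |

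The widest ratio in the assumed range is 95/62 = 1.53. It exceeds the break-even in every row except 33.3% observed with 70% disclosure. A mild imbalance is easily cancelled: at 90% against 80% participation and 33.3% observed, the true value is 30.8% with full disclosure but 34.3% with 90% disclosure.

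**Bounds without assumptions about who declines.** With overall response *r*, the share who would report IPV lies between *p* × *r* and *p* × *r* + (1 − *r*). For *p* = 1/3:
- *r* = 62%: 20.7% to 58.7%.
- *r* = 95%: 31.7% to 36.7%.

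These bounds cover non-response only. Concealment by respondents is a separate matter.

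**The case against.** The strongest defence is context. The sentence closes a paragraph about under-reporting, speaks of respondents, and is hedged by the word *likely*. Read as a remark on concealment alone, it is sound. That reading stands, and it is the reading the fix should make explicit. As printed, however, the conclusion is about the true estimate and carries no such limit.

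The protocol also gives real grounds for a downward lean. Two of its three named selection and coverage effects lower the estimate. The requirement that a woman can separate from whoever accompanies her plausibly excludes some victims. First contact avoids naming abuse or violence, which should reduce refusal prompted by the topic. These make the lean a reasonable judgement but do not establish it: informed consent still precedes the questionnaire, and the authors themselves list refusal by non-victims.

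The numbers deserve caution too. The 62% and 95% are overall response rates from cited studies, not rates by IPV status, so pairing them as a victim/non-victim contrast is purely illustrative. With 70% disclosure, even that contrast leaves the true value (37.2%) above an observed 33.3%.

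Stronger readings are tempting, and the documents do not support them:
- *The true prevalence is lower than observed, or the sentence is simply false.* Nothing shows this; downward biases are listed as well.
- *The upward bias is concealed, or the analysis is bound to a lower-bound rule.* The bias is disclosed in the same section, and Data Analysis plans proportions with confidence intervals and contains no such rule.
- *Using two screening tools "to ensure that we are identifying all probable cases of IPV" inflates the estimate through false positives.* This is possible, but no error rates are given, the tools were chosen partly for specificity, and overall prevalence is described as combining direct questions on three kinds of abuse. The point does not need it.

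Finally, bounds and sensitivity scenarios commonly sit in an analysis plan that is not shown. Their absence is not the finding; the sentence the protocol does print is.

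**Conclusion.** The inference "we will have confidence that the likely 'true' estimate is even higher" is not justified as worded. It follows for under-reporting by respondents, all else equal. Once the protocol's own selection effects are admitted, the net direction is unknown.

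Under the assumed participation range and full disclosure, an observed 33.3% is compatible with a true value from 24.6% to 43.4%, and an observed 5% with 3.3% to 7.5%. Partial disclosure shifts these ranges upward without settling the direction, except where concealment is heavy relative to the imbalance in participation.

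Severity is moderate to minor. Sample size, data collection and planned analyses are untouched. The comparison with surgeons' perceptions does not rest on the sentence. In the Sample Size section, 87% of surgeons put prevalence below 1% and almost all the rest at 5% to 10%. If one third is again observed, even the lower non-response bound at 62% response, 20.7%, exceeds both. At an observed 5%, the 3.3% scenario still exceeds 1%, though not the 5% to 10% band. What changes is whether the study may call its estimate conservative.

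**What to change.** 1. In Protecting Against Sources of Bias, limit the sentence to under-reporting by respondents, or delete it.
2. State there that selection effects act in both directions and that the net direction of bias is uncertain. Give the direction of refusal by non-victims, as is already done for the two downward effects.
3. Report the primary 12-month prevalence with non-response bounds, overall and per site: all non-participants negative, all positive, and a few differential-participation scenarios crossed with a stated disclosure range. The agree/decline counts come from the screening form. Note beside the table that these bounds do not cover women ineligible for lack of privacy or never approached.

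A correction for misclassification over a stated range of sensitivity and specificity is optional.

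The cost is a wording change and one extra table from data already collected, and a less favourable claim. No additional participants or procedures are needed.

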### Ontario PRAISE Pilot Study

In preparation for the multi-center definitive P.R.A.I.S.E. study, we successfully completed a pilot study in Ontario, Canada at two clinical sites (Hamilton Health Sciences - General Site, Hamilton and St. Michael's Hospital, Toronto). The purpose of the pilot study was to provide estimates of patient enrollment, inform study logistics, and prove feasibility for the definitive study. The patients from the pilot study will not be included in the larger prospective study, as we have made multiple changes to the protocol and questionnaire based on our experience with the pilot study.

Our preliminary pilot work suggests that women presenting to the fracture clinics are experiencing IPV to much greater extents than previously recognized by orthopaedic surgeons. In a sample of 282 women at the two participating sites, we found that over the past 12 months 8.5% of women were physically abused, 30.5% were emotionally abused and 3.2% were sexually abused [15]. One third of women in the pilot study sample had experienced IPV (including physical, emotional and/or sexual abuse) in the past 12 months. Our pilot study also found that 2.5% of women presenting to the fracture clinics with orthopaedic injuries suffered these injuries as a direct result of IPV. The generalizability of our pilot study results to all North American, Australian, and European centers requires confirmation from our proposed larger study.

### Feasibility of the Multicenter Definitive Study

The pilot study helped to inform our enrollment rate as well as inform the study logistics. We enrolled 204 patients over five months at the site in Hamilton, which equates to approximately 40 patients per month. St. Michael's Hospital enrolled 78 patients over 2.5 months, or approximately 30 patients per month. Therefore we believe that sites will enroll between 30 and 40 patients per month and that it will take approximately 10 months of enrollment at each site to complete the pilot study. Therefore, it is feasible to complete the definitive multi-center study within the allotted timeframe.

We also made multiple revisions to the protocol and questionnaire based on our experience with the pilot study. We believe these changes will make the questionnaire easier to complete for participants and also enhance the quality of the data obtained.

### Sample Size

According to a recent survey of orthopaedic surgeons in Canada [7], 87 percent of all respondents believe that the prevalence of IPV within their practice is less than 1 percent, with almost all of the remaining respondents believing that the prevalence of IPV in their practice is between 5 percent and 10 percent. Using an estimated IPV prevalence of 5 percent within orthopaedic clinics and standard statistical formulae for estimating sample size of prevalence studies, we have calculated that a sample size of 278 women is necessary for our study to provide an estimate of IPV prevalence with a 95 percent confidence interval between 2.78 percent and 8.31 percent. If the point-estimate of IPV prevalence within orthopaedic clinics is higher than 5 percent, the proportion of the margin of error relative to the estimated prevalence will be lower. To be adequately powered within each region or demographic, each site will therefore recruit 300 participants. The total sample size for the study will be 3,600 participants across the 12 participating centers.

### Data Analysis

Data will be analyzed using SPSS Version 17.0 [SPSS, Chicago, IL] and will be stratified according to clinical center, at which point descriptive statistics can be reported for each site and overall. Dichotomous data will be reported as number of participants and proportions, with corresponding confidence intervals to estimate precision. Continuous data will be presented as means and medians with standard deviations. We will provide descriptive statistics describing the patient demographics and injury characteristics across each clinical site. We will also report the results of the WAST and PVS across each clinical site for IPV prevalence in the past 12 months. These two screening tools will be scored according to the developers guidelines. Finally, we will report descriptive statistics, with 95% confidence intervals, across each clinical site on patient's previous experiences, knowledge, and perceptions with regards to approaching health care professionals about IPV. We will use Chi-square tests (dichotomous variables) or t-tests (continuous data) to determine if there are differences in IPV prevalence across different clinical sites and jurisdictions.

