### Inclusion and Exclusion Criteria

All women who present to a recruiting orthopaedic or trauma clinic will be screened for eligibility. Our inclusion criteria for this observational study are: 1) The patient presents to the fracture clinic for her own appointment; 2) The patient is 16 or 18 years of age or older; 3) The patient is able to read and write well enough to complete the study questionnaires; 4) The patient is being seen at the fracture clinic for the treatment of an orthopaedic injury; and 5) The patient is able to separate herself from anyone who accompanied her to the fracture clinic to complete the questionnaire in privacy. Clinical sites may include patients who are over the age of 16 years in the study if it is permitted by their Research Ethics Board. Some sites may not allow patients under the age of 18 to participate. Lowering the age requirement to 16, where possible, will improve the generalizability of the study and will allow us to determine the rates of IPV in a younger demographic.

The exclusion criteria for this study are: 1) The patient is considered too ill or injured to participate in the study; and 2) The patient is cognitively impaired and unable to participate in the study.

Similar inclusion and exclusion criteria have been used in other studies that sought women's experience with IPV [1,3,8,16]. Once a patient is deemed eligible, she will be invited to participate in the study by a female study coordinator. We will track the number of patients screened and their reasons for ineligibility.

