### Recruitment Rate

For the multi-center definitive P.R.A.I.S.E. study we aim to recruit 3,600 participants across 12 sites in North America, Europe, and Australia. The pilot study helped to inform our enrollment rate proving feasibility of the definitive trial whereby both clinical sites in the pilot study enrolled at least 30 patients per month (St. Michael's Hospital with 30 participants per month and Hamilton Health Sciences - General Site with 40 participants per month). Consecutive patients will be recruited from fracture clinics across North America, Europe, and Australia and based on the results of our pilot study we anticipate that each site will be able to enroll 300 patients within ten months.

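### The plain chi-square test across jurisdictions ignores variation between sites, so its false-positive rate exceeds 5% whenever sites differ

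*Protocol article*

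**What the plan says.** The Data Analysis section names the tests for between-group comparisons: "Chi-square tests (dichotomous variables) or t-tests (continuous data) to determine if there are differences in IPV prevalence across different clinical sites and jurisdictions". Stratification by center appears in the same section, but it is tied to descriptive reporting for each site and overall. No site term or clustering adjustment is attached to the jurisdiction test.

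On structure, the Sample Size section says "each site will therefore recruit 300 participants" and "The total sample size for the study will be 3,600 participants across the 12 participating centers". The Recruitment Rate section says "we aim to recruit 3,600 participants across 12 sites in North America, Europe, and Australia". How many sites fall in each region is not given. The Participating Centers section says sites will be drawn from differing trauma populations, from inner-city to rural.

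The outcome is binary: under Primary and Secondary Outcome Measures, a woman counts as positive if she reports physical, emotional or sexual abuse. Chi-square is therefore the test that the rule assigns to prevalence.

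**The concern.** Women are nested in sites, and sites are nested in jurisdictions. A chi-square on jurisdiction totals treats all the women in a region as independent draws from one common prevalence. If sites within a region differ, the regional proportion is more variable than the binomial formula allows. The test then compares regions with too small an error term, and ordinary site-to-site differences can be read as a regional effect. The protocol expects such differences, because it seeks sites in different settings.

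At stake is a reported regional difference in abuse prevalence that reflects only which clinics happened to represent each region. The Discussion intends the results to support education and a professional position statement, so an overconfident regional contrast could mislead that use. The named test is fixed in the protocol text and is not a detail left open.

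**Working it through.** **The plan's own figure.** The Sample Size section starts from "Using an estimated IPV prevalence of 5 percent within orthopaedic clinics" and gives 278 women with a 95% interval of 2.78% to 8.31%. The exact (Clopper-Pearson) interval for 14/278 = 5.04% is 2.78% to 8.31%, so the figure reproduces. It concerns the precision of one estimate and not a comparison between regions. The total also reproduces: 12 × 300 = 3,600. (Methods/Design mentions ten sites. The results below depend on the 300 women per site, so that discrepancy does not change them.)

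**Inputs.**
- Women per site: 300 (Sample Size).
- Prevalence: 5% (Sample Size) and one third (the pilot study section). Both were tried.
- Significance level: not stated for the tests. Assumed 5% two-sided, in line with "we will report descriptive statistics, with 95% confidence intervals, across each clinical site".
- Sites per jurisdiction: not stated. Splits of 4/4/4, 8/2/2 and 6/6 assumed.
- ICC: not stated. Range 0 to 0.01 assumed for the table.

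**Formula.** With m women per site, the variance of a pooled jurisdiction proportion is inflated by DEFF = 1 + (m − 1) × ICC = 1 + 299 × ICC. When jurisdictions have equal true means, the actual level of the nominal 5% test is P(χ² > critical value / DEFF).
- Three jurisdictions (2 df, critical value 5.991): the level is exp(−2.996 / DEFF).
- Two jurisdictions (1 df, critical value 3.841): the level is P(χ² on 1 df > 3.841 / DEFF).

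Example at ICC 0.005: DEFF = 1 + 299 × 0.005 = 2.495, and exp(−2.996 / 2.495) = exp(−1.201) = 0.301.

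The between-site standard deviation implied by an ICC is √(ICC × p × (1 − p)). At p = 1/3 and ICC 0.005 this is √(0.005 × 0.222) = 0.033, or 3.3 percentage points.

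| Assumed ICC | DEFF | Site SD, p = 1/3 (points) | Site SD, p = 5% (points) | Level, three jurisdictions | Level, two jurisdictions |
|---|---|---|---|---|---|
| 0 | 1 | 0 | 0 | 5.0% | 5.0% |
| 0.001 | 1.299 | 1.5 | 0.7 | 10.0% | 8.5% |
| 0.0025 | 1.748 | 2.4 | 1.1 | 18.0% | 13.8% |
| 0.005 | 2.495 | 3.3 | 1.5 | 30.1% | 21.5% |
| 0.01 | 3.990 | 4.7 | 2.2 | 47.2% | 32.6% |

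**Simulation check** (beta-binomial site effects, 12 sites of 300, 20,000 replicates).
- At ICC 0, rejection is 4.8% to 5.2%.
- Three jurisdictions: 9.8% to 10.3% at ICC 0.001, 17% to 18% at 0.0025, 29.4% to 30.6% at 0.005, and 46.7% to 47.6% at 0.01. The 4/4/4 and 8/2/2 splits give nearly the same result.
- Two jurisdictions (6/6): 8.3% to 8.4%, 14%, 21.2% to 21.6%, and 32.4% to 32.5% at the same ICCs.
- Both prevalences were simulated and agree, except at ICC 0.0025, which was simulated at one third only.

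**The site comparison.** One 12 × 2 chi-square (11 df) across identical sites rejects 4.8% of the time at prevalence 5% and 5.0% at one third. Its level is correct.

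**After the fix.** An F-test of three jurisdictions on the 12 site proportions (four sites each; 2 and 12 − 3 = 9 df) rejects 4.0% to 5.2% of the time for ICCs from 0.001 to 0.05.

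**The case against.** The strongest reply is that inflation is not automatic. If prevalence is the same at every site, the jurisdiction test holds its 5% level. Inflation needs real site variation within jurisdictions, and the protocol gives no ICC from which to size it; at 0.001 the level is only 8% to 10%. This stands, and it is why a range is given. It does not remove the point, because the protocol deliberately seeks unlike sites, and a site spread of 2 to 3 percentage points around a prevalence of one third already gives roughly 14% to 30%.

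The comparison is also secondary. Research Objectives and Hypotheses lists no site or jurisdiction contrast, and the two reasons given under Participating Centers for a multicenter study are a first prevalence report and generalizability. This stands too, and it lowers the severity.

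A reader might go further in four ways that the protocol does not support.
- *The site test is inflated as well.* It is not. Site is the factor being tested, women are independent given site, and the 11-df test keeps its level.
- *Twelve sites mean 66 unadjusted pairwise tests.* Testing all pairs at 5% would give at least one false difference in 71% to 73% of studies, but the protocol does not say that pairs will be tested.
- *A t-test will be applied to prevalence.* The sentence reserves t-tests for continuous data, and prevalence is binary. What remains is a wording flaw: a two-sample t-test cannot compare more than two groups at once.
- *Unequal age limits invalidate the comparisons.* The protocol discloses that "Some sites may not allow patients under the age of 18 to participate" and gives its reasons. Age is collected, and nothing in the document allows an effect to be sized.

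**Conclusion.** The concern holds for the jurisdiction comparison only. As written, the test leaves out between-site error and gives overconfident results whenever sites within a jurisdiction differ. With three jurisdictions the false-positive rate doubles to about 10% at an ICC of 0.001 and reaches 47% at 0.01. With two it runs from about 8% to 32-33% over the same range.

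These figures rest on assumed ICCs, assumed splits of sites, equal site sizes of 300 and a 5% test level. They do not show that a spurious regional finding is more likely than not: within the tabulated range the rate stays below one half. The primary 12-month prevalence estimate is outside this point. Severity: moderate, for a stated rule on a secondary comparison that wording alone can correct.

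**What to change.** Replace the single sentence on tests in the Data Analysis section with three rules.
1. **Sites:** one omnibus chi-square over all 12 sites (11 df).
2. **Jurisdictions:** a test that uses between-site error, either logistic regression with jurisdiction as a fixed effect and site as a random intercept, or an F-test on the site-level proportions. The F-test is the option whose level was checked above.
3. **Continuous variables over more than two groups:** ANOVA or a mixed model in place of the t-test. This is a minor wording correction.

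The number of sites in each jurisdiction should be stated alongside.

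The change needs no new data and no additional participants. Its cost is apparent power: the site becomes the unit of replication for jurisdiction contrasts, so three jurisdictions are compared on 12 site values and not on 3,600 women. That loss reflects the information actually available on regional differences.
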